## Abstract

Spatial navigation (SN) has been reported to be one of the first cognitive domains to be affected in Alzheimer’s disease (AD), which occurs as a result of progressive neuropathology involving specific brain areas. Moreover, the epsilon 4 isoform of apolipoprotein-E (APOE-ε4) has been associated with both sporadic and familial late-onset AD, and patients with mild cognitive impairment (MCI) due to AD are more likely to progressively deteriorate. Spatial navigation performance will be examined on a sample of 76 community-dwelling senior citizens (25 healthy controls; 25 individuals with subjective cognitive decline (SCD); and 26 patients with MCI due to AD) via a virtual computer-based task (i.e., the AppleGame) and a naturalistic task (i.e., the Detour Navigation Test—modified version) for which a wearable device with sensors will be used for recording gait data and revealing physiological parameters that may be associated with spatial disorientation. We expect that patients with MCI due to AD and APOE-ε4 carriers will show altered SN performances compared to individuals with SCD and healthy controls in the experimental tasks, and that VR testing may predict ecological performance. Impaired SN performances in people at increased risk of developing AD may inform future cognitive rehabilitation protocols for counteracting spatial disorientation that may occur during elders’ traveling to unfamiliar locations. The research protocol has been approved by the Ethics Committee of the Istituto Auxologico Italiano. Findings will be published in peer-reviewed medical journals and discussed in national and international congresses.

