### 2.4. Statistical Analysis

Data distribution will be first checked on collected variables by assessing skewness and kurtosis values, by performing normality and heteroscedasticity tests, and by visually inspecting histogram and Q–Q plots. Based on data meeting or non-linear model assumption, either parametrical or non-parametrical analyses will be performed. By means of the R marco *pwr* [86], the minimal sample size has been set as 76 participant, based on a power analysis for a multiple regression model that took into account the following parameters: α = 0.05; 1-β = 0.9; *f*^2^ = 0.15 (medium effect size, in order to be conservative) [87]; and numbers of predictors: 3 (age, APOE genotypes, and belonging to each group, with the last two predictors as dummy variables).

We will detect the route disorientation scores, i.e., WTs and MsH, as already described in Puthysserypaddy et al. [64]. Accordingly, all the violations in terms of deviations from the pre-established return path (i.e., movement at an intersection onto a different path as compared to the original one, or non-roadable walkways) will be written down by the experimenter as WTs in a pre-set paper grid for *Route A*. The overlaps with the *Route A* return path, and, likewise, non-roadable walkways will be written down by the experimenter as WTs in a pre-set paper grid for Route *B*. Further, we will detect the MsH as the participant either slows down/stops and looks around to aid orientation or verbally admits to the experimenter that he/she is unsure about his/her whereabouts, both for *Route A* and the *Route B* return path.

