In addition to the experimenter visually identifying and recording the frequency of the MsH with a stopwatch and a pre-set paper grid, we will measure this variable more objectively using the Howdy Senior integrated accelerometer. For this purpose, we will use the motion sensor of the sensorial body measuring the individual’s linear acceleration in the three axes (i.e., x, y, z). To segment the magnitude signals, according to Schaat et al. [88], we will adopt time intervals of 10 s, with an overlap of 5 s between subsequent intervals because a 10 s segment is sufficiently long to capture multiple steps during walking, thus revealing important behavioral changes. In this way, we will detect the MsH as a signal flattened along the three axes. Further, given that physiological parameters may alter depending on the MsH, we will also investigate the relationship between step variability and co-occurring time-dependent cardiac and respiratory parameters detected by the Howdy App, expressed as mean values, via Pearson’s correlation coefficients or their non-parametric equivalent (i.e., Spearman’s rank order correlation). Moreover, we will run a one-way ANOVA (or its non-parametric equivalent) to compare performances of the three subgroups on gait parameters collected through the Aptive app and the SSNC questionnaire. In order to explore potential association between specific neurocognitive functions and SN impaired abilities, Pearson correlations or their non-parametric equivalent (i.e., Spearman’s rank order correlation) will be further performed between the AppleGame/DNT-mv results and the neuropsychological tests used in the sending centers, especially visual–constructive skills and executive functions (see Appendix A). Given the difference of the neuropsychological battery used in the sending centers, we will group tests according to the primary cognitive domain involved and we will divide the scores obtained in a dichotomous way for each participant according to the reported cut-off values in the test manuals, i.e., 0 = pathological performance; 1 = normal performance.

Finally, a linear/generalized linear regression analysis will be run, taking into account the drop errors of the AppleGame subtasks—considered one at a time—as independent variables, and the total number of “wrong turns” (WTs)/total number of “moments of hesitation” (MsH) (in seconds) of the DNT-mv as dependent variables.

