## 3. Discussion

In relation to the first endpoint, we expect that patients with MCI due to AD will show significantly more SN deficits than healthy controls and individuals with SCD, both in the AppleGame and in the DNT-mv, in terms of higher drop errors on BPI, LPI, and PPI and higher amounts of WTs and MsH, respectively. Virtual and ecological deficits may reflect a cognitive inefficiency of the entorhinal cortex, where AD neuropathology manifests early [25]. It has also been demonstrated that virtual and ecological SN tasks can detect the SN alteration of amyloid-positive MCI patients [89,90]. According to Colmant et al. [91], we also presume that APOE-ε4 carriers will report a PPI deficit in the VR task differently from non-carriers, regardless of subgroup.

Furthermore, we also anticipate that significant physiological parameters modifications (particularly, respiratory function) may be particularly associated with MsH, given that anxiety rather than depression significantly influences SN abilities in non-demented elders [92]. Starting from difficulties in spatial orientation evaluated in naturalistic experiments able to modify gait [93], we finally assume that patients with MCI due to AD will perform worse than SCD and healthy controls in terms of “Time” and “Speed”, and report significant differences in “Direction”, all variables collected by the Howdy Aptive app in the open-space naturalistic task.

In relation to the second endpoint of the research, we assume that the drop errors obtained in the VR task may predict the route disorientation scores of the naturalistic task. In particular, we expect a causal relationship between the BPI drop error of the AppleGame and the *Route A* return path of the DNT-mv, as well as between the LPI drop error of the AppleGame and the *Route B* return path of the DNT-mv, because they mainly rely on egocentric and on allocentric navigation, respectively. A recent systematic review and meta-analysis [44,94] has outlined that the association of navigational tasks performed in virtual and real environments needs to be deeply clarified. In light of this, we believe that the AppleGame could represent a validated technique with which to detect, in laboratory, early SN deficits in populations at risk of dementia conversion to provide high-quality, time-limited diagnosis. It is a cost-effective tool able to predict real-life SN impairment that should be routinely used in clinical practice.

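### The second-endpoint regression names no covariates across three pooled diagnostic groups, so it can serve prediction but cannot support the causal, task-specific reading in the Discussion

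*Protocol article*

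**What the plan says.** Section 1.7 sets the second endpoint as prediction: whether performance on the laboratory task predicts impairment in a real-world setting.

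Section 2.4 gives the model. It is a linear or generalized linear regression "taking into account the drop errors of the AppleGame subtasks—considered one at a time—as independent variables", with total wrong turns (WTs) and total moments of hesitation as outcomes: "MsH) (in seconds) of the DNT-mv as dependent variables". It names no other predictor and no analysis by group.

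Age, APOE and group do appear in Section 2.4, but only in the model used for the sample size, which lists "numbers of predictors: 3 (age, APOE genotypes, and belonging to each group, with the last two predictors as dummy variables". That model contains no drop error.

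The sample pools three groups (Abstract): "25 healthy controls; 25 individuals with subjective cognitive decline (SCD); and 26 patients with MCI due to AD".

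The Discussion (Section 3) states for the first endpoint that "we expect that patients with MCI due to AD will show significantly more SN deficits than healthy controls and individuals with SCD". It names both tasks: "higher drop errors on BPI, LPI, and PPI and higher amounts of WTs and MsH, respectively". It adds that "APOE-ε4 carriers will report a PPI deficit in the VR task differently from non-carriers, regardless of subgroup". For the second endpoint it goes beyond prediction: "we expect a causal relationship between the BPI drop error of the AppleGame and the" Route A return path, and likewise between the landmark drop error and Route B, on the ground that the pairs rely on egocentric and allocentric navigation respectively.

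**The concern.** By the article's own hypotheses, diagnosis moves the predictor and the outcome in the same direction. In a pooled sample the unadjusted slope then mixes two things: the separation between diagnostic groups, and any link between virtual and real-world errors among people with the same diagnosis. Only the second bears on a mechanism shared by one subtask and one route. MCI patients are expected to be worse on all three subtasks and on the naturalistic test, so diagnosis could make every subtask appear to predict every outcome. If the first-endpoint hypothesis is true, a positive pooled slope is hard to interpret as a causal or task-specific link.

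The article also describes two regression models that share no predictor, one powered and one to be run, and does not say how they relate.

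**Working it through.** **The plan's own figures.** The article gives no expected slope or correlation for this endpoint and no size for the group differences, only their direction. There is therefore no stated figure to reproduce for this point. The nearest is N = 76. With three predictors, f² = 0.15 and α = 0.05, that gives 79.6% power, and 90% needs 99. This is a separate matter and nothing below depends on it.

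**Inputs from the article.** Group sizes 25, 25 and 26 (Abstract); α = 0.05 and f² = 0.15 (Section 2.4); MCI worse on both tasks (Section 3).

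**Assumptions.** Drop error and outcome are normal with SD 1 within groups and have no association within groups. MCI is shifted by d SD on both tasks, with d = 0.5, 0.8, 1.0 or 1.5. Subjective cognitive decline (SCD) sits at zero or at half the MCI shift.

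**Expected pooled correlation.** If V is the variance of the group means over the 76 participants, then r ≈ V / (1 + V).

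- SCD at zero: V = (26/76)(50/76)d² = 0.2251d².
- SCD at half: the mean is (25 × 0.5 + 26)/76 = 0.5066 and the mean square is (25 × 0.25 + 26)/76 = 0.4243, so V = (0.4243 − 0.5066²)d² = 0.1677d².
- Example, d = 1.0 and SCD at zero: r ≈ 0.2251/1.2251 = 0.184.

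A pooled correlation is significant with 74 residual degrees of freedom when |r| exceeds 1.993/√(74 + 1.993²) = 0.226.

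**Simulated rejection rates** (20,000 to 40,000 datasets per case, two-sided 5%). Where two values are shown, separate runs or slightly different SCD positions gave them.

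| MCI shift d | Expected r, SCD at zero / half | Unadjusted slope significant, SCD at zero / half | With two group dummies |
|---|---|---|---|
| 0.5 SD | 0.053 / 0.040 | 7–8% / 6% | about 5% |
| 0.8 SD | 0.126 / 0.097 | 19% / 13% | about 5% |
| 1.0 SD | 0.184 / 0.144 | 36–37% / 24% | about 5% |
| 1.5 SD | 0.336 / 0.274 | 88% / 69–70% | about 5% |

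**Cost of adjustment.** A model with drop error, group (two dummies), age and APOE-ε4 carriage (one dummy, assumed) has five predictors and 76 − 1 − 5 = 70 residual degrees of freedom. For the 1-df test of drop error at partial f² = 0.15, the noncentrality is 0.15 × 76 = 11.4, which gives 91.5% power. With the stricter convention, 0.15 × (1 + 70 + 1) = 10.8, it is 90.0%. The planned N can bear the adjustment.

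**The case against.** The strongest reply is that the endpoint is prediction. For that purpose an unadjusted association across the healthy, SCD and MCI spectrum is legitimate, and where the groups differ on both tasks the pooled association is real, not a false positive. Diagnosis may also mark the same pathology that impairs both tasks, since the Discussion ties the deficits to the entorhinal cortex, so conditioning on it may remove signal of interest. This stands. A reader might infer that the pooled result is invalid or should be demoted to description; Section 1.7 does not support that.

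A reader might also infer that the authors decided against adjustment. The text does not say so. The phrase about taking subtasks singly concerns the subtasks and does not exclude covariates, and the power model shows that age, APOE and group were in mind. What can be said is that the stated regression names none of them and that the two model descriptions need reconciling.

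A third inference, that the second endpoint is positive by construction, fails on size: at a 0.5 SD shift the rejection rate is close to nominal.

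Finally, causal wording appears once, in the Discussion, and adjusting for group would neither make an observational association causal nor by itself test the pairing of subtask with route. That is also right, and it is why the wording needs changing as well as the model. The reply does not rescue the causal, task-specific claim itself, which the stated model cannot separate from diagnosis.

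**Conclusion.** The point holds for the causal and task-specific reading, not for prediction. With no within-group link, diagnosis alone makes the unadjusted slope significant in about 6–8% of trials at a 0.5 SD MCI shift, 13–19% at 0.8 SD, 24–37% at 1.0 SD and 69–88% at 1.5 SD, against about 5% once group is in the model. The problem is slight at 0.5 SD and serious from about 1 SD.

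These figures rest on assumed equal shifts on both tasks, SCD between zero and half the MCI shift, and normal outcomes. Wrong turns are counts, for which the article allows a generalized linear model. Age (Section 1.3 says navigation declines with it, and Section 2.1 enrols ages 65 to 85) and APOE are plausible further shared influences, but their contribution was not quantified and no figure here reflects them.

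**What to change.** 1. Keep the pooled regression in Section 2.4 and label it as the answer to the prediction question.
2. Add a pre-specified second model: outcome on drop error, group (two dummies), age and APOE-ε4 carriage, still with one subtask at a time. State how it relates to the three-predictor model used for the sample size, so that the two parts of Section 2.4 agree.
3. Rest any claim of a link beyond diagnosis on the adjusted drop-error coefficient, and report both estimates side by side.
4. In Section 3, replace causal relationship with association.

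The cost is four degrees of freedom out of 76 and some analysis text. Group, age and APOE are already recorded, and no further participants are needed. The drawback is that adjustment may take out signal that diagnosis shares with both tasks, which is the reason to report both estimates and not the adjusted one alone.

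### The BPI–Route A and LPI–Route B predictions cannot be tested on WT and MsH totals for the whole DNT-mv; route-level outcomes should be named

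*Protocol article*

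**What the plan says.** Section 1.7 sets the second endpoint in general terms: whether performance on the laboratory task predicts impairment in a real-world setting. The Discussion (section 3) repeats this, expecting that "the drop errors obtained in the VR task may predict the route disorientation scores of the naturalistic task". It then becomes specific: "we expect a causal relationship between the BPI drop error of the AppleGame and the *Route A* return path of the DNT-mv", and likewise "between the LPI drop error of the AppleGame and the *Route B* return path of the DNT-mv". The stated reason is "because they mainly rely on egocentric and on allocentric navigation, respectively". Section 2.3.2 describes the two walks in the same way, the first as mainly egocentric and the second as mainly allocentric.

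Section 2.4 defines wrong turns (WTs) separately by route. On Route A they are "deviations from the pre-established return path"; on Route B they are overlaps with the Route A return. Non-roadable walkways count on both. WTs go on a separate grid for each route. Moments of hesitation (MsH) have one definition and are noted on both return paths.

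The regression at the end of section 2.4 enters the three AppleGame drop errors singly as predictors. On the outcome side it has "the total number of “wrong turns” (WTs)/total number of “moments of hesitation” (MsH) (in seconds) of the DNT-mv as dependent variables". No outcome is named for Route A or Route B alone.

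**The concern.** The article fixes a hypothesis at route level and an analysis at whole-test level. If the analysis is run as written, a significant slope of BPI on total WTs could come from Route A, from Route B or from both. It could still be reported as support for the egocentric pairing, which it did not examine. The same holds for LPI and Route B.

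The WT total is also awkward to interpret. A participant who rigidly retraces Route A makes few errors on Route A and many on Route B. One who wanders off the learned path on Route A but finds a genuine alternative on Route B does the reverse. Both can have the same total. What is at stake is the interpretation of the second endpoint's specific claims, not whether the endpoint can be analysed at all.

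**Working it through.** **1. The plan's own design figure.** Section 2.4 gives N = 76 for three predictors, f² = 0.15, α = 0.05 and power 0.90. The noncentral F calculation (u = 3, v = 72, λ = 0.15 × 76 = 11.4) gives power 0.796 at N = 76, and 0.90 needs N = 99. The figure therefore does not reproduce. That is a separate matter and nothing below depends on it; f² = 0.15 and N = 76 are borrowed only for scale.

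**2. Can the total identify a route?** Let X be a drop error and let A and B be the Route A and Route B scores. Let rA and rB be their correlations with X, c the correlation between A and B, and k = SD(B)/SD(A). Then

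corr(X, A+B) = (rA + k·rB) / √(1 + k² + 2ck).

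With k = 1 this is (rA + rB)/√(2 + 2c), so only the sum rA + rB enters. Take c = 0 and r = √(0.15/1.15) = 0.361:

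- effect on Route A only: (0.361 + 0)/√2 = 0.255
- effect on Route B only: (0 + 0.361)/√2 = 0.255
- half of 0.361 on each route: 0.361/√2 = 0.255

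Three different states of nature give the same result on the total. Only the first fits a BPI–Route A link with no Route B component, and only the second fits a Route B link alone. No sample size separates them.

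**3. What the sum mixes.** WTs have three kinds of content: leaving the Route A path (Route A), overlapping the Route A path (Route B), and non-roadable walkways (both). The first two run in opposite directions with respect to the Route A path; the third does not. MsH are defined alike on both routes, so a total of MsH is coherent as a quantity but still loses the route.

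**4. Power, as an illustration.** The article gives no values for c, k or rB, so they are assumed: k = 1, c from -0.3 to +0.3, and rB either 0 or half of rA (0.18). For a single predictor at N = 76, u = 1, v = 74, f² = r²/(1 - r²) and λ = 76·f². On Route A alone, f² = 0.15 gives power 0.915. On the total:

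| rB | c | r on total | f² | power |
|---|---|---|---|---|
| 0 | -0.3 | 0.361/√1.4 = 0.305 | 0.103 | 0.79 |
| 0 | 0 | 0.361/√2 = 0.255 | 0.070 | 0.62 |
| 0 | +0.3 | 0.361/√2.6 = 0.224 | 0.053 | 0.51 |
| 0.18 | -0.3 | 0.542/√1.4 = 0.458 | 0.265 | 0.99 |
| 0.18 | 0 | 0.542/√2 = 0.383 | 0.172 | 0.95 |
| 0.18 | +0.3 | 0.542/√2.6 = 0.336 | 0.127 | 0.87 |

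Summing can cost much power, cost little, or gain some, depending on rB. The attribution problem in step 2 is present in every row.

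**The case against.** The strongest reply is that the total does test the second endpoint as section 1.7 defines it, and that the route pairings are a further expectation added in the Discussion. That stands. A reader might infer that the endpoint itself goes untested; the documents do not support this.

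A reader might also infer that the totals add oppositely defined errors throughout. That is true of only part of the WTs, not of non-roadable walkways or MsH. Nor does it drive the power loss. Rigid retracing implies a negative A–B correlation, which is where the loss is smallest in the table.

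A large power loss is also tempting to claim. It requires BPI to be unrelated to Route B errors, whereas the article says only that each route relies mainly on one strategy.

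Entering the subtasks one at a time may look like a flaw as well. The Discussion expects BPI to relate to Route A and LPI to Route B; it does not say that either is the exclusive or stronger predictor. Single-predictor models can test those two associations once the outcome is split.

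Finally, the word total might mean a total within each route, and an article may leave detail to a fuller plan. The wording attaches the totals to the DNT-mv and names no route, so the per-route reading is the weaker one. The article also states its outcome outright, so this is a mismatch between two stated things and not an omission.

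**Conclusion.** The concern holds in a limited form. As written, the regression can address whether drop errors predict overall disorientation on the DNT-mv. It cannot address whether BPI relates to the Route A return or LPI to the Route B return. That conclusion needs no numerical assumption.

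The effect on power is indeterminate from the document: about 0.51–0.79 or about 0.87–0.99 on the total, against 0.915 on Route A alone, under the two assumed values of rB with equal variances. These figures treat the scores as continuous and should not be presented as a finding about this study's power. The point is worth correcting before analysis, since the mismatch affects what the study may claim and the remedy is small.

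**What to change.** In section 2.4, make Route A WTs, Route B WTs, Route A MsH and Route B MsH separate dependent variables. Name BPI with the Route A outcomes and LPI with the Route B outcomes as the tests of the specific hypotheses. Keep the DNT-mv totals for the general prediction question. If per-route totals were intended all along, one clarifying phrase is enough.

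No new data are needed: WTs already go on a grid for each route, and MsH are noted on both return paths. The plan as written implies six models (three subtasks × two outcomes). The named pairings add four (two pairings × WTs and MsH), ten in all. The multiplicity burden is small; the text should say how the four are handled, or that they are read without adjustment.

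A joint model of the subtasks, or a BPI-versus-LPI contrast, is optional. It is needed only if the authors wish to claim that one subtask is the specific predictor for a route.
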